### Setting and participants

Subjects are recruited from three HIV comprehensive care clinics (CCC) in Kenya. One facility is an urban university-run clinic situated in a lower socioeconomic area of Nairobi, the second is an urban clinic attached to a faith-based hospital situated in a middle income area of Nairobi, and the third is a government-run clinic situated in a vast rural district of Kenya populated by pastoralists.

Patients are eligible to participate if they are initiating HAART for the first time (within two weeks before or after enrolment screening), if they are adults (at least 18 yrs old), if they owned or had sufficient access to a mobile phone (shared access is allowed if access is daily and the phone owner agrees to participate), and if they were able to sufficiently operate a cell phone to communicate using text-messaging (help by a partner is sufficient for illiterate subjects). Patients need to provide oral and written consent to participate. For patients who are illiterate, clear oral consent is obtained. Patients are excluded if they do not meet inclusion criteria or are not planning to attend the enrolment clinic for the planned study period (at least two years). Patients are considered newly initiating HAART if they have not taken HAART in at least one year and have not taken it ever for more than 2 months. Most prevention of mother to child transmission (PMTCT) regimens in Kenya include limited antiretroviral regimens and not true HAART, so participation in PMTCT is not an exclusion criteria. Therefore, the study covers a broad range of patients attending comprehensive care clinics (CCC) for ART in Kenya.

Participants are compensated for their participation time with money for lunch on study visit days (100 Kenya shillings). Patients are not provided cell phones or network airtime credit.

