#### Secondary outcomes

The potential benefits of the intervention are quite broad, so multiple secondary outcomes are of interest and were selected through academic collaboration. The secondary outcomes fall under the categories of health, quality of life, social factors, and economic indicators (see Table 1). The primary purpose of taking antiretroviral medications for HIV infection is to maintain or restore health in someone who is HIV infected. Several other factors that contribute to a subject's prosperity or overall well-being may be affected directly (by way of enhanced support mechanisms associated with the intervention), or indirectly (through improvements in health related to HAART effect). We therefore feel it is important to assess each of these outcomes independently.

**Table 1 T1:** Secondary Outcome Measures

**Secondary outcome measures (6 months and 12 months post initiation of HAART)**	**Type**
*Health outcomes*	
Self-reported adherence as a percentage	Binary
Suppressed HIV viral load (in copies)	Continuous
Immune reconstitution (change in CD4 T cell count from baseline)	
Time to virological failure	Continuous
Weight gain [lbs] and BMI	Time-to-event
Occurrence of opportunistic infections (OIs)	Continuous
Time to reporting of adverse drug events (ADEs)	Binary
Deaths (all cause)	Time-to-event
*Quality of life (QOL)*	Time-to-event
SF-12	
Satisfaction with care provided	Continuous
*Social factors*	Continuous
Level of disclosure of HIV status	
Impression of stigma	Binary
Family dyamics	Continuous
*Economic factors*	Continuous
Employment attendance	
Household member school attendance	Continuous
Cell phones lost/stolen	Continuous

HAART = highly active antiretroviral therapy, SF-12 = short form 12 adapted for regional application in Kiswahili.

In addition, we hypothesize that the intervention will lead to improved retention on ART.[5] Because participants are actively traced for twelve month follow-up visits, we will use composite retention outcomes. We define 'retained' as someone who followed-up on their scheduled visit without being traced and is still taking ART versus 'unretained' which includes subjects who stopped taking ART before their twelve month visit, who are lost to follow-up, or required active tracing after missing their scheduled twelve month appointment. We will report each element of the composite endpoints.[6]

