### Sample size

The primary objectives of this trial to improve adherence to HAART and suppression of HIV viral load evaluated at 12 months. The sample size calculation is based on the comparison between proportions of patients with adherence rates (measured as percent of adherence >95%) in the two groups at 12 months because this is the variable that required the larger sample size. The criterion for significance (alpha) has been set at 0.05. The test is 2-tailed, which means that an effect in either direction will be interpreted.

The sample was calculated using (Cary, NC). With the proposed sample size of 247 and 247 for the two groups (ie assuming a 1:1 allocation ratio), the study will have power of 80% to yield a statistically significant result using a chi-squared test (assuming an intention-to-treat principle for the analysis) at alpha = 0.05/2 (ie using the Bonferroni correction factor for the two primary outcomes).

This computation assumes 10% improvement in 'perfect adherence' over a baseline of 75% determined from rates in a large adherence trial by AMPATH in Western Kenya which we felt is the most representative data available. [7] This difference of 10% was selected as the smallest difference that would be important to detect, in the sense that any smaller difference would not be of clinical or substantive importance. It is also assumed that this difference is reasonable, in the sense that an effect of this magnitude could be anticipated in this field of research.

Assuming attrition rates of approximately 10% we intend to over-enrol by 10% resulting in an enrolment target of at least 534 participants for randomization (267 in the Intervention, and 267 in the Control).

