#### Statistical methods

The intervention arm (SMS) will be compared against the control (SOC) for all primary analysis. We will use chi-squared test for binary outcomes, and T-test for continuous outcomes. For subgroup analyses, we will use regression methods with appropriate interaction terms (respective subgroup × treatment group). Multivariable analyses will be based on logistic regression (See Table 2) for binary outcomes and linear regression for continuous outcomes. We will examine the residual to assess model assumptions and goodness-of-fit. For timed endpoints such as mortality we will use the Kaplan-Meier survival analysis followed by multivariable Cox proportional hazards model for adjusting for baseline variables. We will calculate Relative Risk (RR) and RR Reductions (RRR) with corresponding 95% confidence intervals to compare dichotomous variables, and difference in means will be used for additional analysis of continuous variables. P-values will be reported to four decimal places with p-values less than 0.001 reported as p < 0.001. Up-to-date versions of SAS (Cary, NC) and SPSS (Chicago, IL) will be used to conduct analyses. For all tests, we will use 2-sided p-values with alpha = < 0.05 level of significance. We will use the Bonferroni method to appropriately adjust the overall level of significance for multiple primary outcomes, and secondary outcomes.

To assess the impact of potential clustering for patients cared by the same clinic, we will use generalized estimating equations [GEE] (ref) assuming an exchangeable correlation structure. Table 3 provides a summary of methods of analysis for each variable. Professional academic statisticians ([name]) blinded to study groups will conduct all analyses.

**Table 3 T3:** Variables, Measures and Methods of Analysis

**Variable/Outcome**	**Hypothesis**	**Outcome Measure**	**Methods of Analysis**
1) **Primary**	Intervention improved outcome from baseline to 6 months		
			
a) Adherence at 12 months		Percent adherence in previous 30 days >95% [binary]	Chi-squared test
			
b) Suppression of HIV viral load at 12 months		Viral load ≤400 copies/ml [binary]	Chi-squared test

2) **Secondary** Adherence percentage at 12 months	improvement occurred	Adherence % (>95%) [binary]	Chi-squared test

HIV viral load at 12 months	improvement occurred	Viral load (copies)	T-test

Immune reconstitution (change in CD4 T cell count from baseline)	improvement occurred	Cd4 T-cells/mm^3 ^(continuous)	T-test

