Time to virological failure	Improvement occurred	Virological failure after successful suppression	Kaplan-Meier survival analysis

Weight gain [lbs] and BMI	improvement occurred	Change in weight (lbs) and BMI [continuous]	T-test

Occurrence of opportunistic infections (OIs)	improvement occurred	Presence of AIDS defining opportunistic infection [binary]	Chi-squared test

Time to reporting of adverse drug events (ADEs)	improvement occurred	Presence of drug-related adverse event [time to event]	Kaplan-Meier survival analysis

Deaths (all cause)	improvement occurred	All-cause mortality [binary]	Chi-squared test and Kaplan-Meier survival analysis

SF-12	improvement occurred	Quality pf life questionnaire [continuous]	T-test

Satisfaction with care provided	improvement occurred	Questionnaire [continuous]	T-test

Level of disclosure of HIV status	improvement occurred	Disclosed to a family member [binary]	Chi-squared test

Impression of stigma	improvement occurred	Questionnaire [continuous]	T-test

Family dyamics	improvement occurred	Questionnaire [continuous]	T-test

Employment attendance	improvement occurred	Questionnaire [continuous]	T-test

Household member school attendance	improvement occurred	Questionnaire [continuous]	T-test

Cell phones lost/stolen	improvement occurred	Presence of cellphone [binary]	Poisson regression

Stopped taking HAART	improvement occurred	Self-report [binary]	Chi-squared test

Required active tracing for 12 month follow-up	improvement occurred	Field officers [binary]	Chi-squared test

3) **Subgroup Analyses:**			Regression methods with appropriate interaction term
Urban vs. rural	Distance affects adherence		
Female vs. male	Sex affects adherence		
Phone ownership (owned vs. shared)	Ownership affects adherence		
Level of education	Low education affects adherence		

4) **Sensitivity Analyses:**	improvement occurred	All outcomes	
a) Per protocol analysis			a) Chi-squared/T-test test
b) Adjusting for baseline covariates			b) Multivariable regression
c) clustering among individuals within a clinic			c) GEE

IMPORTANT REMARKS:

• The GEE[11] is a technique that allows to specify the correlation structure between patients within a hospital and this approach produces unbiased estimates under the assumption that missing observations will be missing at random. An amended approach of weighted GEE will be employed if missingness is found not to be at random.[12]

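### Table 3: the name, measure and method of the lost/stolen phone outcome do not match, and a binary phone-presence measure does not capture loss or theft

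*Protocol article*

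**What the plan says.** Table 1 of the protocol article (Secondary outcomes) includes "Cell phones lost/stolen" among the economic factors. Table 3 (Statistical methods) repeats that name, gives the outcome measure as "Presence of cellphone [binary" and the method as "Poisson regression". The hypothesis cell says only that improvement occurred.

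The text of Statistical methods sets the general rules:

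- Tests: "We will use chi-squared test for binary outcomes, and T-test for continuous outcomes".
- Adjusted models: "Multivariable analyses will be based on logistic regression (See Table 2) for binary outcomes".
- Effect measures: "We will calculate Relative Risk (RR) and RR Reductions (RRR) with corresponding 95% confidence intervals to compare dichotomous variables".

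Poisson regression appears nowhere else in the article, and no variance estimator is named for it. Under Setting and participants, patients are eligible "if they owned or had sufficient access to a mobile phone (shared access is allowed if access is daily", with the owner's agreement. The article gives no expected rate for phone presence, loss or theft.

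**The concern.** The row raises two separate problems.

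The first is what is measured. Loss or theft is an event during follow-up and can happen more than once. Presence of a phone is a status at one visit and runs in the opposite direction. An analyst who follows the measure cell does not answer the question that the outcome name asks.

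The second is how it is analysed. A Poisson model suits a count of losses, which is what the name suggests, but the measure cell says binary. Fitted to a yes/no variable with its default variance, a Poisson model overstates the standard error, and badly so when the coded event is common. Phone access is an entry criterion, so presence at follow-up could well be common. At stake are the meaning of this secondary outcome and, under some readings, the width of its confidence interval and the power of its test.

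**Working it through.** **Step 1. Compare the row with the rest of Table 3.** Eight other rows are tagged binary: the two primary outcomes (adherence, viral suppression) and six secondary ones (adherence above 95%, opportunistic infections, deaths, disclosure, stopping HAART, active tracing). All eight name the chi-squared test; deaths adds Kaplan-Meier. The phone row is the only binary row without it. Its cells are intact in the text, so this is not a broken table. Table 1's type column is displaced in the text available, so nothing here rests on it.

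**Step 2. Compare the measure with the name.**

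| Situation at follow-up | Lost/stolen? | Phone present? |
|---|---|---|
| Phone lost, then replaced | yes | yes |
| Own phone lost, now shares one | yes | probably yes |
| Two phones lost, third in use | yes, twice | yes |
| Phone sold or shared access ended | no | no |
| Original phone kept | no | yes |

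Only the last row gives the two definitions the same reading.

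**Step 3. Size of the variance effect.** The plan states no figure for this outcome, so there is none to reproduce. For proportions p1 and p0 with n per arm, the standard error (SE) of the log ratio is

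- model-based Poisson: sqrt(1/(n·p1) + 1/(n·p0))
- binomial (correct for a yes/no outcome): sqrt((1−p1)/(n·p1) + (1−p0)/(n·p0))

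At p1 = p0 = p the ratio is 1/sqrt(1−p), and n cancels. The proportions below are assumptions.

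| Proportion coded as the event | SE ratio, model-based to binomial |
|---|---|
| 0.02 | 1.01 |
| 0.05 | 1.03 |
| 0.10 | 1.05 |
| 0.20 | 1.12 |
| 0.75 | 2.00 |
| 0.80 | 2.24 |
| 0.90 | 3.16 |
| 0.95 | 4.47 |

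With a robust variance the ratio is 1.00 throughout.

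**Step 4. The same data, coded both ways.** Take the planned enrolment, "534 participants for randomization (267 in the Intervention, and 267 in the Control", and suppose a phone is present in 246 of 267 and 235 of 267.

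- Presence as the event: log ratio ln(246/235) = 0.0457. Model-based SE = sqrt(1/246 + 1/235) = 0.0912, p = 0.62. Robust SE = sqrt(1/246 − 1/267 + 1/235 − 1/267) = 0.0288, p = 0.11. Ratio 3.17.
- Absence as the event (21 and 32 of 267): log ratio ln(21/32) = −0.421. Model-based SE = sqrt(1/21 + 1/32) = 0.281, p = 0.13. Robust SE 0.267, p = 0.11. Ratio 1.05.
- Chi-squared test without continuity correction, either coding: p = 0.11.

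The chi-squared test does not depend on which level is coded as the event. The model-based Poisson test does, and the row does not say which level is meant.

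**Step 5. Effect on power, for illustration.** Assume 80% against 90% present, 267 per arm, two-sided 0.05 before any Bonferroni adjustment, and power = Φ(|log ratio|/SE − 1.96).

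- Presence coded: log ratio ln(0.9/0.8) = 0.118. Model-based SE 0.0940 gives about 24%; binomial SE 0.0368 gives about 89%.
- The complement coded, 20% against 10%: log ratio ln 2 = 0.693. Model-based SE 0.237 gives about 83%; binomial SE 0.221 gives about 88%.

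**The case against.** A reader might infer that following the row must give standard errors several times too large and a nearly powerless test. The article does not support that. The result needs three conditions together: presence is the modelled event, presence is common, and the model-based variance is used. The outcome's own name points to the opposite coding, no prevalence is given, and no variance estimator is stated. In a condensed article that last detail is reasonably left to a fuller analysis plan, so its absence is not a fault. Poisson regression with a robust variance is a recognised way to estimate a relative risk from a binary outcome, and relative risks are what the plan intends for dichotomous variables. Poisson regression is therefore not wrong in itself for this row.

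There are further mitigating points. The plan separately promises relative risks with confidence intervals for dichotomous variables. It also promises residual and goodness-of-fit checks, which could expose the underdispersion of a common binary variable fitted as a count. The power figures use unadjusted 0.05, whereas the plan applies Bonferroni to the secondary outcomes, so absolute power would be lower under any method.

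All of this stands, and it limits the size of the numerical problem. It does not reconcile the row. The measure still fails to capture the named outcome, and the method still departs, without explanation, from the plan's rule for binary outcomes.

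**Conclusion.** The point holds as a mismatch of name, measure and method in one row of Table 3. Two parts need no assumption: a binary presence measure cannot identify a phone lost and replaced or count repeat losses, and Poisson regression contradicts the stated rule for binary outcomes and the practice in the eight other binary rows.

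The effect on precision is conditional. The standard error is 2.2 to 4.5 times too large only with presence coded as the event, an assumed 80% to 95% prevalence and a model-based variance. It is 1% to 12% too large with loss or theft as the event at an assumed 2% to 20%, and not inflated with a robust variance. Where inflation occurs it widens intervals and loses power; it does not create false positives. Severity is low: this is one secondary outcome among many, with no bearing on the primary outcomes.

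**What to change.** Rewrite the Table 3 row in one of two ways and carry the same definition into Table 1:

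- **Count.** Define the outcome as the number of phones lost or stolen since baseline. Keep Poisson regression, with an offset for follow-up time and a robust variance, and report a rate ratio.
- **Binary.** Define the outcome as any phone lost or stolen since baseline (yes/no). Use the chi-squared test and report the relative risk with its confidence interval, as for the other binary outcomes. Poisson regression with a robust variance would also serve.

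In either case, state that loss or theft is the event, and say how a shared phone is handled.

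The cost is one table row plus a check that loss or theft is recorded. The questionnaires are not shown. The study log covers phone access, but weekly contact takes place only in the intervention arm, so a log-based count could be more complete there. The follow-up questionnaire, used at the 6 and 12 month visits, would be the more even source. If it already asks about loss or theft, no new data are needed.

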### Randomization

A project statistician generated 1:1 randomization numbers for study arm assignments using a random number generating program. The randomization was stratified in a 2:2:1 ratio to the three clinics (the rural clinic having the lower number of assignments). Written allocation of assignment is sealed in individual opaque envelopes marked with study identification numbers which are distributed to all three study clinics in sufficient quantity to allocate the target numbers of participants. After consenting to participate and meeting inclusion criteria, screened subjects are enrolled and immediately afterward are assigned to the randomized study arm by a clinician opening the sealed envelopes to determine allocation. Age, gender, and CD4 T cell counts will be assessed for balance of study arm allocation at each site.

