### Data collection

Data collection tools include a baseline questionnaire, follow-up questionnaire (used at 6 and 12 month visits), the SF-12 quality of life assessment adapted for local content, GPS co-ordinates of the clinics and participants homes, and a household roster of economic indicators. Questionnaires include continuous and categorical variables and Likert scales. All questionnaires were designed in English and translated to Kiswahili then back translated to verify meaning. Questionnaires are administered by clinic staff fluent in the languages of participants. In instances where study participants speak only local languages, the clinician translates questions directly. Antiretroviral adherence is assessed at each follow-up visit by inquiring about missed doses in the previous 30 days and calculating percent adherence according to pill counts. A visual analogue scale is used to confirm calculated adherence rates. A weekly study log is kept to record the weekly SMS messages and responses including details related to phone access, medication adherence and health or illness issues as they arose. Telephone communications with subjects in the control arm are also recorded in a similar study log, even though they are not sent the weekly SMS messages. Clinic charts are reviewed for WHO stages and clinical data on health parameters and events. A study register is kept to record follow-up.

Attempts are made to obtain lab data from samples obtained at usual clinical care time points and thus are either collected at the same visit as the study questionnaires are administered or within two weeks if not the same day. The CD4 T cell counts are run on a FACScan (Becton Dickson) at a centralized site. Plasmas for HIV viral load testing (Roche Amplicor) are separated at the central laboratory for the Nairobi clinics, but separated and frozen at -20C and batched for transport from the rural district clinic. All plasmas are frozen at -80C at the central lab. Viral loads are run in batches using manufacturer controls.

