#### Sub-group analyses

Because a large clinical trial on this type of intervention has never been done before, we are interested in the interventions effect on various subgroups and the effect of multiple covariates on treatment outcomes. Subgroups of particular interests and potential covariates proposed are outlined in Table 2. Treatment arms will be compared with respect to potential covariates using continuous and categorical univariate analyses.

**Table 2 T2:** List of subgroups and potential covariates

**Subgroups of interest**	**Potential covariates**
Urban vs. rural	Age
By clinic	Gender
Female vs. male	Distance from clinic
Phone ownership (owned vs. shared)	Income level
Occupational designation	Cost to attend clinic
Level of education	Level of literacy
Usual mode of transportation used	Baseline quality of life
	HIV staging
	Level of disclosure of status
	Crossover into intervention

HAART = highly active antiretroviral therapy.

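### Table 3 tests its distance hypothesis with urban versus rural × treatment, which is in effect one clinic against two and cannot isolate distance, although individual distance can be computed

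*Protocol article*

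**What the plan says.** Table 3, item 3 of the protocol article (Statistical methods) pairs the urban versus rural subgroup with the hypothesis "Distance affects adherence". For subgroups the same section states: "we will use regression methods with appropriate interaction terms (respective subgroup × treatment group".

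Under Setting and participants, two clinics are urban and in Nairobi, one university-run and one faith-based, and "the third is a government-run clinic situated in a vast rural district of Kenya populated by pastoralists". Under Randomization: "The randomization was stratified in a 2:2:1 ratio to the three clinics (the rural clinic having the lower number of assignments".

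Among the items collected are "GPS co-ordinates of the clinics and participants homes" (Data collection). Table 2 (Sub-group analyses) lists "Distance from clinic" as a potential covariate and has a separate subgroup by clinic. No subgroup or hypothesis row uses individual distance.

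**The concern.** The row names distance but tests location. The article's only urban and rural labels are those of the clinics, so the contrast is naturally the one rural clinic against the two urban ones. That clinic also differs in operator, population and staff. If SMS works differently there for any such reason, the row would report it as an effect of distance. Two patients of the same clinic, one living near and one far, count as identical.

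There is a second mismatch. Read literally, the hypothesis concerns a main effect: do distant patients adhere less well? The planned term is an interaction: does the SMS effect differ by location? These are separate questions. At stake is a secondary but useful result, namely whether distance matters for adherence and whether SMS helps distant patients more or less. The trial collects the data to address both directly.

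**Working it through.** **Inputs.** The article states no power or error figure for this row, so there is none to reproduce. From the document: enrolment target 534; clinics 2:2:1; adherence 75% in control and 85% with SMS (Sample size); for all tests "we will use 2-sided p-values with alpha = < 0.05 level of significance". Assumed, because the document gives nothing: every distance and clinic effect below, the spread of distance, and the urban–rural gap.

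**Step 1, the contrast.** 534 × 2/5 = 213.6 and 534 × 1/5 = 106.8, so about 214, 213 and 107 patients. With T for treatment and R for the rural clinic, the planned model is

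logit P(adherent) = a + bT + gR + dRT, with test of d = 0.

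Distance does not appear. The term d is the SMS effect at the rural clinic minus that at the urban clinics, on the logit scale.

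**Step 2, sizes on the logit scale.** Planned SMS effect: ln(0.85/0.15) − ln(0.75/0.25) = 1.735 − 1.099 = 0.636. If SMS does nothing at the rural clinic, d = −0.636. If it lowers adherence there from 75% to 65%, the rural effect is 0.619 − 1.099 = −0.480, so d = −0.480 − 0.636 = −1.116.

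**Step 3, distance has no effect.** Simulated trials, 1,500 per setting, logistic Wald tests (Monte Carlo standard error at most √(0.25/1500) = 1.3 points):

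| Rural clinic differs in | Planned R × T rejects | Clinic-adjusted distance tests reject |
|---|---|---|
| adherence level only, −0.3 / −0.5 / −0.8 logit | 5% / 5% / 5% | 4–6% |
| SMS effect, −0.65 / −1.0 / −1.3 logit | 24% / 52% / 77% | 5–6% |

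An absent SMS effect (−0.636) therefore gives about 24%, and a reversed one (−1.116) about 60%. A main-effect contrast of rural against urban would reject 20%, 52% and 91% of the time in the first row, but that is not the planned subgroup test.

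**Step 4, distance affects adherence equally in both arms** (−0.4 logit per within-clinic SD), with rural mean distance 0, 0.5, 1 or 2 SD larger:

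| Test | 0 | 0.5 | 1 | 2 |
|---|---|---|---|---|
| Planned R × T | 4% | 5% | 6% | 6% |
| Distance main effect, adjusted for treatment and clinic | 95% | 95% | 96% | 97% |
| Treatment × distance, with clinic and clinic × treatment | 4% | 5% | 4% | 5% |

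Neither interaction tests the literal hypothesis. The main-effect term does.

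**Step 5, distance modifies the SMS effect** (−0.6 logit per SD), same gaps:

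| Test | 0 | 0.5 | 1 | 2 |
|---|---|---|---|---|
| Planned R × T | 5% | 9% | 22% | 64% |
| Treatment × distance, with clinic and clinic × treatment | 76% | 75% | 79% | 78% |

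**Step 6, wider gaps.** Take log-normal distance with log SD 0.8. A 2 SD gap is then a rural median exp(1.6) ≈ 5 times the urban one, and an eight-fold gap is ln 8 / 0.8 = 2.6 SD. At eight-fold, if the SMS effect falls by 0.6 logit per log-km, R × T has about 67–69% power against 56–60% for the direct term. If it rises by 1.0 per log-km, R × T has about 45–65%, depending on the distance at which the planned 75% to 85% effect is taken to apply, against about 94%.

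**The case against.** The strongest reply is that this is a loose label on an exploratory row in a condensed article, and that distance is already in the plan. Much of that stands.

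- A reader might infer that the row rejects whenever the rural clinic has lower adherence. The documents do not support that: the planned term is an interaction and stays near 5% in that case.
- A reader might infer that a real distance effect would largely be missed. As to modification of the SMS effect, this holds for gaps up to about 1 SD. For a wide gap, which a vast rural district makes possible, the planned term can match or beat the direct one when the SMS effect weakens with distance. Even then the result cannot be separated from clinic.
- A reader might infer that distance goes unanalysed. It does not: it is a Table 2 covariate, and the multivariable models refer to that table. But no row ties its coefficient to the distance hypothesis, and covariate adjustment does not show whether distance modifies the SMS effect.
- The on-site freezing of plasma at the rural clinic might be counted as a further confounder. It bears on viral load, not on self-reported adherence.
- The article never says whether urban and rural refer to the clinic or to residence. One clinic against two is the natural reading, not a stated definition.
- Clinic has its own subgroup row, and a GEE analysis for clustering is planned. Neither measures distance.

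The objection does not remove the core. Table 3 states a hypothesis and a test that do not match, which is different from leaving detail to another document.

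**Conclusion.** The point holds in limited form and is minor. The urban versus rural × treatment test does not test whether distance affects adherence: its power for a pure distance effect is about 5% at every gap tried. As a test of whether distance modifies the SMS effect it is confounded with clinic. With no distance effect at all, it rejects about 24% of the time if SMS does nothing at the rural clinic and about 60% if the effect is reversed there. Detecting such a difference is a legitimate purpose of a subgroup test; attributing it to distance is the error.

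These sizes rest on assumed effects, on 534 analysed patients, and on urban and rural following the clinic. The power comparison also rests on an urban–rural distance gap that the article does not give. The primary comparisons are untouched.

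**What to change.** In Table 3, move the distance hypothesis from the urban versus rural row to individual log home-to-clinic distance computed from the GPS data, and report two terms:

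1. The main effect of log distance, adjusted for treatment and clinic, for whether distance affects adherence.
2. Treatment × log distance, with clinic and clinic × treatment in the model, for whether distance modifies the SMS effect.

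Keep urban versus rural as a descriptive clinic contrast, define whether it follows clinic or residence, and state that with one rural clinic it cannot be attributed to distance.

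The cost is one table row and two regressions on data already collected. Missing home coordinates will need handling. Power is modest if the effect is small: with log SD 0.8, about 57% for a main effect of −0.3 logit per log-km, and 56–57% for an interaction of 0.6 per log-km.
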